### 11b. Criteria for discontinuing or modifying allocated interventions for a given trial participant

If staff or caretakers believe a child is not responding to treatment, they will be evaluated for medical complications. A more detailed clinical assessment with the potential for inpatient treatment will be available to all patients who develop medical complications and/or are not responding to treatment.

If a participant wishes to be removed from the study, their information will no longer be collected and they will be given the option to continue with the treatment they are currently receiving. If a participant does not wish to receive any treatment, counselling will be given to encourage the caretaker to keep the child in treatment until he/she is fully recovered.

**11c. Strategies to improve adherence to intervention protocols**

Participants will be given a one-on-one counselling session at admission to emphasize the importance of completing treatment, as well as practicing optimal hygiene and infant and young child feeding. Participants will be asked to return used RUTF packets on a weekly basis to monitor adherence and minimize the risk that RUTF packets are sold.

Trained community health workers will follow-up with absent patients to counsel caretakers who may be experiencing difficulties bringing their child to the clinic. Patients who miss 3 consecutive visits will be considered a defaulted participant. Children in both the intervention and control groups will be followed up in the same manner.

All participants in both the intervention and control groups will be referred to the nearest mother-to-mother or father-to-father support groups during and after treatment. The support groups offer health education and social support to caretakers of malnourished and at-risk children.

### 11d. Relevant concomitant care and interventions that are permitted or prohibited during the trial

Routine health care that can be treated on an outpatient basis will be provided to all children per the national CMAM protocol. Any child with a medical complication and/or not responding to treatment will be referred to the Stabilization Center for a medical evaluation. Inpatient care will be offered to those who require it for as long as needed. If a child is admitted for inpatient care, they will be discharged as a referral and exit from the study.

## Outcomes

Table 6: Primary and Secondary Outcomes

|  | **Measurement variable** | **Analysis metric** | **Method of aggregation** | **Time point** |
| --- | --- | --- | --- | --- |
| Primary | | | | |
| Recovery | MUAC ≥125mm and no oedema  Note: The definition of recovery in both the control and intervention groups will be defined as two consecutive measurements with a MUAC≥125mm and no oedema. For the purposes of analysis, children receiving the standard protocol will be considered as cured when their MUAC≥125mm and no oedema for two consecutive measurements, even if they continue to receive treatment until they reach a WHZ >-2. | Final value | Proportion | End of treatment |
| Secondary | | | | |
| Coverage | % of children eligible for treatment (MUAC<125mm) who receive it  Note: The coverage surveys will be based on a MUAC-only definition of Global Acute Malnutrition (GAM (MUAC<125mm). Weight and height measurements will not be taken. | Final value | Proportion | Semi-quantitative evaluation of access and coverage (SQUEAC) survey (after final enrolment) |
| Defaulter | Child discharged as defaulter (3 missed visits) | Final value | Proportion | End of treatment |
| Died | Child died during treatment | Final value | Proportion | End of treatment |
| Length of stay | Days in treatment | Duration of time | Sum | End of treatment |
| Average daily weight gain | grams/kilograms/day | Daily | Mean | End of treatment |
| Average daily MUAC gain | mm/day | Daily | Mean | End of treatment |

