## Objectives

Primary objective: Determine the impact of the Combined Protocol on recovery compared to the standard treatment of OTP and SFP (recovery defined as achieving ≥125mm MUAC).

Secondary objectives: Determine the impact of the Combined Protocol on coverage, defaulting, length of stay, death rate, average daily weight gain and average daily MUAC gain compared to the standard treatment of OTP and SFP.

Hypothesis: The treatment of acute malnutrition using the Combined Protocol will be as effective as the standard protocol at recovering children from malnutrition as indicated by program exit status, length of stay, and average weekly weight and MUAC gain. Coverage of SAM and MAM treatment will increase under a Combined Protocol by improving early detection of MAM and preventing deterioration into SAM, and by improving program coherence and reducing loss during the transition from OTP to SFP.

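### Table 6 summarises length of stay by a sum, which is not a per-child comparison, and counts days to the end of treatment instead of to analysis-defined recovery

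*Protocol*

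**What the plan says.** Section 12 (Outcomes), Table 6, gives the length-of-stay row as "Length of stay | Days in treatment | Duration of time | Sum | End of treatment". The fourth column is headed as the method of aggregation. Recovery, coverage, default and death carry a proportion there. Weight gain and MUAC gain carry a mean, for example "Average daily MUAC gain | mm/day | Daily | Mean | End of treatment". Length of stay is the only row with a sum.

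Section 7 (Objectives) makes length of stay a between-arm secondary outcome: "Determine the impact of the Combined Protocol on coverage, defaulting, length of stay, death rate, average daily weight gain and average daily MUAC gain". The hypothesis then uses it as evidence of effectiveness, "as indicated by program exit status, length of stay, and average weekly weight and MUAC gain".

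Several exits end a child's days in treatment before recovery. Table 6 has rows for default, "Child discharged as defaulter (3 missed visits", and for death, "Child died during treatment". Section 11d adds inpatient transfer: "If a child is admitted for inpatient care, they will be discharged as a referral and exit from the study". The length-of-stay row does not say how these exits count. The recovery row of the same table provides that standard-arm children count as cured at two consecutive MUAC measurements of at least 125 mm without oedema, even where treatment continues until WHZ is above -2.

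**The concern.** A between-arm comparison of length of stay needs a figure per child. A group total also carries the number of children in the arm, so two arms with identical stays give different totals whenever enrolment differs.

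A second problem would remain if the sum were simply replaced by a mean. Days to the end of treatment are not days to recovery. An early default, death or referral cuts the count short, so an arm with more of these can appear to have a shorter stay although no child recovers sooner. In the other direction, a standard-arm child kept in treatment for WHZ after meeting the analysis definition of cure adds days that the Combined Protocol arm has no matching rule to add. Since the hypothesis reads length of stay as a sign of how well children recover, either effect could mislead on this secondary outcome.

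**Working it through.** The protocol gives no figure for length of stay, so there is none to reproduce. The durations and default shares below are assumptions, except where a source is named.

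**Inputs**
- Children per arm: 12 clusters x 150 recruited = 1,800 (section 14).
- Stay of children who do not default: 60 days in both arms (assumed).
- Default share d: 10% in one arm, 20% in the other (assumed).
- Day of default exit E: 20 to 80 (assumed). Table 6 does not say which date closes a defaulter's stay. Where visits are every 14 days, three missed visits take 3 x 14 = 42 days to accrue, so late values are possible.

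**Step 1. Dependence of a total on enrolment**

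Total = N x 60. With 1,800 children it is 108,000 child-days. With an assumed 1,650 it is 99,000. The difference is -9,000/108,000 = -8.3%, although each child stays 60 days in both arms. If both arms reach 1,800 the difference is zero, and a total and a mean then give the same relative comparison.

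**Step 2. Effect of early exits at equal enrolment**

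All-exit mean = (1 - d) x 60 + d x E, and total = 1,800 x mean. Moving d from 0.10 to 0.20 changes the mean by 0.10 x (E - 60).

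| E (day) | Mean, d = 10% | Mean, d = 20% | Total, d = 10% | Total, d = 20% | Change |
| --- | --- | --- | --- | --- | --- |
| 20 | 56.0 | 52.0 | 100,800 | 93,600 | -7.1% |
| 28 | 56.8 | 53.6 | 102,240 | 96,480 | -5.6% |
| 40 | 58.0 | 56.0 | 104,400 | 100,800 | -3.4% |
| 60 | 60.0 | 60.0 | 108,000 | 108,000 | 0% |
| 80 | 62.0 | 64.0 | 111,600 | 115,200 | +3.2% |

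The relative change is the same for the total and the all-exit mean. Changing the sum to a mean therefore removes the dependence on enrolment in step 1 but leaves this one.

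**Step 3. Check with non-recovered children separated**

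Take recovered children at 60 days, early exits at day 20 and non-recovered children at 112 days (the 16-week limit in Table 2, used for both arms for simplicity).
- 85% recovered, 10% early exit, 5% non-recovered: 0.85 x 60 + 0.10 x 20 + 0.05 x 112 = 58.6 days, total 105,480.
- 75%, 20% and 5%: 0.75 x 60 + 0.20 x 20 + 0.05 x 112 = 54.6 days, total 98,280.

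The measure falls by 7,200/105,480 = 6.8%, while time to recovery among those who recover is 60 days in both cases.

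**Step 4. Days after analysis-defined cure**

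Table 2 discharges Combined Protocol children on MUAC and oedema, with a minimum stay. Tables 3 and 4 also admit and discharge on WHZ, and Table 6 acknowledges that standard-arm children may stay on for it. This lengthens days in treatment by a route open in the standard arm only. The protocol gives no basis for its size, so no figure is put on it.

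**The case against.** The strongest reply is that the sum is a within-child quantity. Standard-arm children pass from OTP to SFP, so their two stays have to be added, and the objective clearly has days per child in mind. This reading is possible, though it fits the column less well than the group summaries beside it. If it is right, the enrolment argument falls. The row then lacks any between-child summary, and the end point is still the end of treatment, so the cell needs correcting on either reading.

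A reader might infer that enrolment is bound to distort the comparison. The protocol does not support that. Section 14 sets 150 children per cluster, and the distortion arises only if that target is not met equally. The higher coverage expected in section 7 for the Combined Protocol would, if it raised admissions, lengthen that arm's total and so would not flatter it.

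A reader might also infer that every default or death lowers the figure. Only exits earlier than the stay they replace do so. In the table the effect is nil at day 60 and reversed at day 80. Inclusion of all exits is itself inferred from an unrestricted row, and the detailed handling of exits may properly sit in an analysis plan that is not shown. The aggregation is different, because the protocol fixes it.

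Finally, length of stay is a legitimate programme indicator in its own right, and default and death have their own rows, so a difference in default would be visible beside it. That stands. It does not make days in treatment a sound indicator of how well children recover, which is how section 7 uses it.

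**Conclusion.** The point holds in a limited form. A sum is the wrong aggregation for a between-arm comparison of length of stay: it gives either a total that depends on enrolment or no group summary at all. Days to the end of treatment also differ from days to recovery, because early exits truncate them and standard-arm children may continue after analysis-defined cure.

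Under the assumptions above (60 days for other children, 1,800 per arm, 10% v 20% default), truncation moves the total and the all-exit mean by between -7.1% and +3.2% as default exit runs from day 20 to day 80. Unequal enrolment would add to this: -8.3% for an assumed 1,650 against 1,800.

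It would be wrong to conclude that the trial's main result is at risk. This is a secondary outcome, and neither the primary comparison of recovery nor the sample size depends on it.

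**What to change.** In Table 6, replace the sum with the mean or median number of days per child, OTP and SFP days combined. Count from admission to the date on which the analysis definition of recovery is met, among recovered children, and compare the arms with allowance for clustering by facility.

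Support this with time to recovery in all enrolled children, treating default, death and referral as competing events. It is needed because the recovered-only summary conditions on an outcome that treatment may affect. If total days in treatment are still wanted as a programme indicator, report them per child under that name and state which exits count and on what date a default ends the stay.

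The cost is one table row and one additional analysis. Visit dates and MUAC come from the patient cards and follow-up forms that section 19 already has entered in CommCare, so no new data are needed and no treatment rule changes.

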## Participant timeline

Once the study begins, all existing patients in the health facilities assigned to the intervention will complete treatment per the standard protocol, and all new patients eligible for inclusion will begin treatment per the Combined Protocol.

Enrolment: March- June 2017

SQUEAC: June 2017

Qualitative study: June 2017

End of study: October 2017

## Sample size

The primary outcome, ‘recovery’, in both the control and intervention groups will be defined as two consecutive measurements with a MUAC≥125mm and no oedema. We expect the recovery rate to be 85% based on the average program statistics in Nairobi, Kenya and Aweil East, South Sudan. If the combined protocol is non-inferior to the current protocol, allowing for a 10% non-inferiority margin, then we would require 12 clusters in each arm with 100 children in each cluster to demonstrate non-inferiority of the combined protocol, with 80% power at the 5% level of significance. An intracluster correlation coefficient (ICC) of 0.05 was used, a conservative estimate based on the results of a similar cluster randomized study testing an integrated SAM/MAM protocol in Sierra Leone (Maust et al. 2015).

In order to account for losses to follow-up (estimated as 15%) and cross-overs (estimated as 5% in each arm), 150 children per cluster will be recruited for inclusion in the study. This was determined based on the following calculation:

100 x 1/(1-.15) x (1/(1-.05-.05)²) = 146

Table 7: Sample Size Calculations

| **Assumptions** | **Value** |
| --- | --- |
| Power | .80 |
| Level of significance | .05 |
| Intervention recovery | .85 |
| Control recovery | .85 |
| Margin of Non-Inferiority | .10 |
| One or two-tailed test | 2 |
| Number of facilities per arm | 12 |
| **Individuals per cluster** | **100** |
| **Total individuals** | **2400 (1200 in South Sudan, 1200 in Kenya)** |

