## Trial design

The study will be a prospective, multi-center cluster-randomized controlled (cRCT) non-inferiority trial. The unit of randomization will be health facilities stratified by country and then randomly assigned to the control or intervention group. Children in the control group will receive the standard protocol while those in the intervention group will receive the combined protocol.

The study will include a total of 24 clusters in the following categories:

Kenya

| Arm 1 | Control (6) | Standard protocol |
| --- | --- | --- |
| Arm 2 | Intervention (6) | Combined protocol |

South Sudan

| Arm 1 | Control (6) | Standard protocol |
| --- | --- | --- |
| Arm 2 | Intervention (6) | Combined protocol |

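### The stated 80% power for 12 clusters of 100 per arm holds only under a normal approximation; allowing for 24 clusters it is about 77%, and 78 to 79% at planned recruitment

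*Protocol*

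**What the plan says.** Section 14 (Sample size) gives the design and the claim together: "we would require 12 clusters in each arm with 100 children in each cluster", "with 80% power at the 5% level of significance". The inputs are in the same section and its Table 7:

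- Recovery: "We expect the recovery rate to be 85" per cent, entered in Table 7 for both arms.
- Margin: "allowing for a 10% non-inferiority margin".
- Sidedness: the table row reads "One or two-tailed test | 2".
- Clustering: "An intracluster correlation coefficient (ICC) of 0.05 was used, a conservative estimate".

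Recruitment is then raised from 100 to 150 per cluster. The section gives the reason as "losses to follow-up (estimated as 15%) and cross-overs (estimated as 5% in each arm".

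Section 8 (Trial design) makes the health facility the unit of randomisation and states "The study will include a total of 24 clusters", six per arm in each country. Section 16a confirms stratification by country. The protocol does not mention a t distribution, between-cluster degrees of freedom, or a cluster added because there are few of them.

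**The concern.** Whole facilities are allocated, so the treatment contrast is a comparison of 12 facilities with 12. The between-facility variance dominates its standard error and has to be estimated from those 24 units. A power formula that uses the critical value 1.96 ignores that uncertainty. With hundreds of clusters the difference would be negligible. With 24 it is a few percentage points.

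Power in a non-inferiority trial is the chance of a conclusive result when the two protocols are truly equal. If it is below the stated figure, the risk of an inconclusive trial is understated: about 23% instead of 20% at the stated cluster size. The result itself will be judged by its confidence interval against the margin, so at stake is a stated design property and not the validity of the conclusion.

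**Working it through.** **Inputs** (section 14 and Table 7; number of facilities also in section 8): p = 0.85 in both arms, so the true difference is 0; margin 0.10; two-tailed 5%, so 0.025 on the non-inferiority side; ICC 0.05; k = 12 clusters per arm; m = 100 children per cluster.

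**Step 1. Reproduce the protocol's figure.**

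- Per arm without clustering: n = (1.960 + 0.842)² × 2 × 0.85 × 0.15 / 0.10² = 200.1, rounded up to 201.
- Design effect: 1 + (100 − 1) × 0.05 = 5.95.
- Clusters per arm: 201 × 5.95 / 100 = 11.96, so 12, with nothing added for few clusters.
- SE = √(2 × 0.85 × 0.15 × 5.95 / 1200) = 0.0356, and 0.10 / SE = 2.812.
- Normal power: Φ(2.812 − 1.960) = 80.3%.

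This matches the stated 12 clusters and 80%. The alternatives tried do not: a one-sided 5% test needs 9.4 clusters per arm, a superiority comparison of 85% with 75% needs 14.9, and adding one cluster per arm for small numbers gives 12.96, so 13.

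**Step 2. Same inputs, allowing for 24 clusters.** Power = P(T > t), where T is non-central t with non-centrality 0.10 / SE and t is the 97.5% point on the available degrees of freedom. There are 24 − 2 = 22 degrees of freedom for two arms. Allowing for country leaves 21, or 20 if each country-by-arm cell has its own mean. On 22 the critical value is 2.074 instead of 1.960.

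| Analysed per cluster | Design effect | 0.10 / SE | Normal | t, 22 df | t, 21 df | t, 20 df |
| --- | --- | --- | --- | --- | --- | --- |
| 100 | 5.95 | 2.812 | 80.3% | 76.7% | 76.5% | 76.3% |
| 127.5 (150 less 15%) | 7.325 | 2.862 | 81.6% | 78.1% | 77.9% | 77.7% |
| 150 | 8.45 | 2.890 | 82.4% | 78.9% | 78.7% | 78.5% |

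**Step 3. Check by simulation.** In 200,000 simulated beta-binomial trials with 12 clusters per arm, a cluster-level t test on 22 df showed non-inferiority in 77.0% of trials at 100 per cluster, 78.1% at 127 and 79.1% at 150.

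**Step 4. What would reach 80%.** Extra children in the same facilities add little at this ICC: with 12 clusters per arm, about 200 analysed per cluster would be needed (80.0%, 22 df). Thirteen clusters per arm at 100 each give 80.2% (24 df). These figures show the size of the gap and are not proposals.

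**Step 5. Could a z-based analysis recover the 80%?** If the statistic follows a t distribution on 22 df, comparing it with 1.96 gives a one-sided error of about 3.1% instead of 2.5%. The 80% is then bought with significance, and the protocol claims both together.

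**The case against.** **The arithmetic is right for the method used.** This stands. The stated figure reproduces, so there is no slip in calculation. The fault is a method that leaves out the small number of clusters.

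**The trial recruits 150 per cluster, not 100.** This stands in part. A reader might infer that the trial as planned has only 77% power. The documents do not support that: 77% belongs to the 100 per cluster in the power sentence. Under equal recovery in both arms, cross-over does not change the outcome, so about 127 per cluster may be analysed. All 150 are possible if defaulters, who have a recorded exit status, are counted as not recovered. The gap is then 1 to 2 points. It does not close, and section 14 assigns the extra recruitment to loss and cross-over.

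**The primary analysis is not shown.** It may be set out in an SAP. The t-based figure therefore assumes a test on cluster-level degrees of freedom. The assumption is reasonable, because the alternative gives up the stated error rate. Nor is the point about a missing analysis detail: the figure and all its inputs are in the protocol.

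**The gap is small beside the uncertainty in the inputs.** This is true. At 100 per cluster and 22 df, an ICC of 0.045 instead of 0.05 would restore about 80%, and the protocol calls 0.05 conservative. Stratification by country might also remove some variance. But the stated 80% is tied to an ICC of 0.05.

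**Unequal cluster sizes.** A reader might go the other way and infer a larger shortfall, since unequal clusters lower power. The protocol sets one fixed target per cluster and gives no measure of variation in cluster size, so no further loss can be put in numbers.

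**Conclusion.** The point holds, at modest size. On the protocol's own inputs, 80% power and 5% significance are not delivered together. Power falls short of the stated 80% by about 3 to 4 points at 100 analysed per cluster, and by about 1 to 2 points at planned recruitment.

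This rests on four assumptions: an ICC of exactly 0.05, 85% recovery in both arms, equal cluster sizes, and an analysis that holds its two-sided error with 20 to 22 degrees of freedom. That a normal approximation was used is inferred from the exact reproduction, since the protocol names no formula.

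A reader might infer that the trial is seriously underpowered, or that it needs more facilities or a different margin. The documents do not support this: the gap is about what one more cluster per arm would close, and a slightly lower ICC would also close it.

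**What to change.** In section 14 and in the power row of Table 7, replace 80% with about 77% at 100 analysed children per cluster, and add that power is 78 to 79% at planned recruitment (127 to 150 analysed per cluster). State that these figures use a t reference with 22 or fewer degrees of freedom, from 24 facilities, and assume equal cluster sizes.

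Leave the 10-point margin, the number of clusters and enrolment unchanged. The cost is one sentence and one table cell, and a stated power slightly less favourable than before.

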## Recruitment

Prior to randomization of health facilities to either the control or intervention group, community health workers will conduct a sensitization campaign across the communities that fall within the catchment area of the 12 facilities in each country. The goal of the campaign will be to meet with community leaders and encourage them to send malnourished children to the clinics for treatment. Randomization of the facilities will occur prior to the start of the trainings of the field teams, as research officers will only be trained on the protocol they are to implement. Screening to detect malnourished cases will take place after the randomization, since referral of children to the facilities cannot begin until the teams are trained and in place and ready to provide services. Community health workers will conduct screenings in an equivalent manner across the catchment areas of both arms of the study. All malnourished children (i.e. MUAC <125mm) will receive a referral slip and their caretaker will receive instructions on how to access treatment. For any medically complicated cases requiring immediate treatment, IRC/ACF will provide transportation to the nearest stabilization center.

Patients who present to health facilities on their own will also be screened for inclusion. Weight and height measurements will be taken at the health facility only (in addition ot MUAC measurements), per national and international guidelines. All patients eligible to participate in the study based on the inclusion and exclusion criteria will be invited to enrol in the study.

In Nairobi, Kenya in 2015 the average monthly enrolment at each health facility of children classified with acute malnutrition according to the primary study definition of <125mm MUAC is 30. It is expected it will take four months to reach the sample size in Nairobi.

In Aweil East, South Sudan in 2015 the average monthly enrolment at each health facility of children classified with acute malnutrition according to the study definition of <125mm MUAC is 80. It is expected it will take two months to reach the sample size in Aweil East.

Using the above averages, enrolment is expected to take a minimum of four months, with an additional 4 months for completion of treatment of the last enrolled child. Therefore the study is expected to take 8 months.

Enrolment will occur over a period when malnutrition tends to be at its highest.

